# Effectiveness of an Educational Intervention in Reducing New International Postgraduates’ Acculturative Stress in Malaysian Public Universities: Protocol for a Cluster Randomized Controlled Trial

**DOI:** 10.2196/12950

**Published:** 2020-02-27

**Keywords:** acculturative stress, acculturation, international students, adjustment, protocol, cluster, randomized controlled trial

## Abstract

**Background:**

Universities around the world, including Malaysia, have attracted many international students from different countries. Research has reported that acculturative stress resulting from international students’ attempts to adjust to the cultures of host countries is one of the most challenging issues that affects their lives in general and academic lives in particular.

**Objective:**

This study aims to examine the effectiveness of an educational intervention on acculturative stress among new postgraduate international students joining Malaysian public universities.

**Methods:**

A cluster randomized controlled trial design with Malaysian public universities as the unit of randomization will be used in this study. Public universities will be randomized in a 1:1 ratio to be either in the intervention (educational program) or control group (waiting list). Participants in the intervention group will receive 7 sessions in 9 hours delivered by an expert in psychology and the researcher. The control group will receive the intervention once the 3-month follow-up evaluation is completed.

**Results:**

The data will be analyzed using the generalized estimation equation with a confidence interval value of 95%; significant differences between and within groups are determined as *P*<.05. The results of the study underlie the effectiveness of educational program in decreasing acculturative stress of new international students and enabling them to cope with a new environment. The results of this study will contribute to previous knowledge of acculturative stress, acculturation, and adjustment of international students. Furthermore, such results are expected to play a role in raising university policy makers’ awareness of their postgraduate international students’ acculturative stress issues and how they can help them avoid such stress and perform well in their academic life.

**Conclusions:**

We expect that the intervention group will score significantly lower than the wait-list group on the immediate and 3-month postintervention evaluation of acculturative stress and achieve a higher level of adjustment. Results will have implications for international students, policy makers at universities, the Malaysian Ministry of Higher Education, and future research.

**Trial Registration:**

Clinical Trials Registry India CTRI/2018/01/011223; http://ctri.nic.in/Clinicaltrials/showallp.php?mid1= 21978&EncHid=&userName=[name]

**International Registered Report Identifier (IRRID):**

PRR1-10.2196/12950

## Introduction

### Background

Previous research has identified the challenges and needs of international students during their higher education outside their native countries [1-6]. The most challenging issue faced by international students is adaptation to the new environment, especially the new culture of the host country [7-10]. Other challenges include difficult living circumstances; different foods, climate, cultural norms, and customs [2,8,11-14]; and stressful interactions with local students and the host environments [15]. International students also face academic or educational challenges such as an unfamiliar educational system and language barriers [2,8,11,16]. These stressors can lead to a kind of stress commonly referred as acculturative stress, defined as a psychological and physical discomfort experienced by an individual in a new cultural environment [17].

A causality relationship between a high level of stress experienced by international students and deteriorating health conditions and even more serious health problems has been reported [18,19]. The combination of lack of social relations, financial support, and stress results in students’ feelings of anxiety [5], depression, physical illness, and wasted potential [20-22], leading to depression [23], negatively affecting their academic achievements [24], reducing their academic performance, and even leading them to drop out of university [22,25], especially when it becomes excessive [19]. In this regard, preventing student dropout is a challenging task in higher educational institutions [26]. Pal [27] suggested that programs should be employed in higher educational institutions to address student levels of stress and intention to drop out. Furthermore, research has indicated there is a significant positive relationship between acculturative stress, social support, and sociocultural adjustment of international students [28]. Other studies reported a positive relationship between acculturative stress and psychological adjustment [29,30]. Acculturative stress was found to have a negative relationship with positive acculturation. Acculturative stress is negatively correlated with social support. Consequently, lower levels of acculturative stress are associated with both positive cultural associations and higher levels of social support [31], and acculturation is negatively associated with acculturative stress [32]. In terms of students’ social support and their adjustment, studies on international students in the Malaysian context [32-34] and overseas [28,35] reported that social support significantly affects international students’ adjustment by lowering the level of stress. Similarly, studies have found that social support has positive impacts on sociocultural adaptation as it acts against the stress of cultural adaptation of international students [36,37].

Malaysia has attracted many international students, which has positioned it 11th in world ranking in hosting international students [38]. The increasing number of international students coming from other regions, including the Middle East [39], and the plan to increase intake to 250,000 students by 2025 (Malaysia Education Blueprint 2015-2025: Higher Education) raises the need for enhancing the quality of services and enabling higher educational institutions to meet the needs and requirements of the students, especially in health care. The number of international students has increased from 18,242 to 83,633 in the years 2001-2013, however, making this a challenge. In addition, while the government aims to make the country of Malaysia an international hub for higher education excellence by 2020, research on international postgraduates is still limited. There are only a few studies on international postgraduates that explore the challenges they face in academic and social adjustment in Malaysia [40,41]. Cross-cultural adaptation is crucial for postgraduates in order to overcome the various challenges and become able to psychologically and socioculturally adapt to the new environment [42]. Acculturative stress is caused by stressors such as language barriers, academic barriers, racial discrimination [43,44], perceived surrounding environment, attitudes toward the host country among international postgraduate students [45], cultural shock, homesickness, and perceived hatred [46]. While Rajab et al [46] found that international students’ acculturative stress is moderate, Par et al [47] reported that almost 40% of international postgraduate students joining Malaysian universities experience a high level of acculturative stress, which could affect their academic achievement in higher educational studies [48].

Although the above studies in Malaysia are useful for investigation of international students’ acculturative stress, these studies have focused on describing stress merely from student perception and self-reported reflections, and they are scant and general in comparison with those studies carried out in other host countries [49]. For instance, while research on international student acculturative stress and adaptation has reached its third phase of development in other host countries like Australia [50], in the Malaysian context, such research is still in the early phase of development [49]. In addition, studies in the Malaysian context have ignored the importance of implementation of stress coping interventions. Further empirical investigations into issues pertaining to international student requirements are needed to enable students to improve achievement and performance in higher educational institutions [51]. Based on the above issues, gaps addressed in earlier research, and the need to address stress and adjustment in international students, our study proposes an educational intervention program that can assist international postgraduates to cope with and overcome the different aspects of acculturative stress.

### Theoretical and Conceptual Frameworks

The literature highlights several acculturation models developed by scholars over time, one of which is the bidirectional model of acculturation widely accepted in previous research [52]. Specifically, Berry’s model of acculturation [53] places emphasis on two distinct aspects: the person’s identification with their native culture and identification with the host culture. However, early views and perspectives of acculturation can be valuable in theoretically explaining and discussing the process of acculturation. According to the first view, acculturation is seen as a term covering issues resulting from first-hand contact of individuals with people of different cultural backgrounds. This view also stresses that the consequence of acculturation is changes in the individual’s native or original cultural patterns and behaviors. Based on this view, there is a distinction between acculturation and cultural change in the sense that acculturation encompasses such cultural change as one of its aspects, and assimilation, which is at times a phase of acculturation [54].

The second view emphasizes acculturation as a cultural change initiated by the conjunction of two or more autonomous cultural systems. Thus, acculturative change can result from direct cultural transmission or it can be a result of noncultural aspects, including modification of ecological or demographic characteristics by an impinging culture, and it may be delayed. Hence, acculturation can appear in the form of an internal adaption after the individual accepts alien cultural patterns or behaviors or it can emerge in the individual as a kind of reactive adaptation of traditional modes of life [54,55]. In addition, as defined by Graves [56], psychological acculturation is a process of changes taking place in an individual who participates in a culture-oriented contacting situation directly affected or influenced by the new or external culture and by the changing culture to which they belong. According to Redfield et al [57], acculturation comprises various changes in different forms, identified by Berry [58] as biological, social, and physical changes.

Based on the model of stress developed by Lazarus and Folkman [59], Berry [60] and Berry et al [61] developed an acculturative stress model. The main idea of the framework is that acculturative stress results from situations in which a person’s experiences and appraisal become problematic due to the person’s inability to deal with them and failure to adjust to them through behavioral changes. This implies that acculturative stress is a response of the individual to life events which are grounded in the experience of acculturation [54]. However, not all acculturation changes are assumed to lead to acculturative stress because how acculturation is experienced, perceived, and interpreted by the individual can be influenced by moderating and mediating factors, including personal characteristics such as age, gender, and social support prior and during acculturation [53,62].

In their systematic review of the theoretical frameworks used in research on international students’ sociocultural adaptation to host countries between 2012 and 2017, Sarmiento et al [63] found that 82.2% of the research papers and articles provided a description of particular theoretical frameworks on students’ adaptation. Moreover, 69.3% of these articles reported treating nonspecific frameworks. What was interesting in this review paper was that the majority of the reviewed research papers focused on investigation of international students’ issues related to acculturation and adaption based on the acculturation model. Acculturation should also be approached from the perspective of cross-cultural psychology. As pointed out by Berry [64], acculturation should be investigated in its cultural contexts. In such contexts, researchers can obtain a better understanding of the cultures and individuals in contact. Therefore, such investigation seeks to link the acculturation of a given group of people to which an individual belongs and the individual’s psychological acculturation.

Berry’s [65] acculturation model describes cross-cultural adaptation as a process that involves the individual’s or group’s behavioral and psychological changes in life resulting from their contacts with others from different cultures. Whereas psychological changes are related to one’s modified attitudes, perceptions, and beliefs, behavioral changes are pertinent to their external behavior toward those typical of the host society or mainstream [65]. In a previous study, the term psychological dimension was defined as the person’s perceived acculturative stress which was attributed to their cross-cultural adaptation (eg, how they perceived unfamiliar social cultural customs) [66]. On the other hand, psychological adaptation is often associated with the person’s emotional and affective satisfaction about their integration into a new social environment, while sociocultural adaptation encompasses the process in which the person fits in a new environment and effectively interacts with it [63]. Therefore, our study is framed within the theoretical perspective of acculturation and acculturative stress developed by Berry et al [61] and Berry [53] and further expanded by Berry [65,67,68].

### Study Aims

This study aims to develop, implement, and evaluate the effectiveness of an educational intervention in reducing acculturative stress and improving adjustment among new international postgraduates joining Malaysian public universities. Specifically, the study aims to (1) describe participants’ sociodemographic characteristics, acculturation, acculturative stressors, and social support at the baseline; (2) determine the level of acculturative stress, adjustment (psychological and sociocultural), and intention to drop out of university among new international postgraduates at the baseline; and (3) determine the effect of the educational intervention on acculturative stress, adjustment, and intention to drop out between and within the control and intervention groups at the immediate and 3-month postintervention follow-up.

### Study Hypothesis

In order to achieve the above research objectives, the study attempts to test the following null research hypotheses: (1) the intervention group will score significantly higher than the wait-list group on the immediate and 3-month postintervention evaluation of acculturative stress, adjustment, and intention to drop out measures (between groups) and (2) the acculturative stress, adjustment, and intention to drop out scores for the intervention group at the immediate and 3-month postintervention follow-up will be significantly higher than scores of the baseline or preintervention (within groups).

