### Participants

Public universities that will be eligible to participate in the study should satisfy the following criteria: acting or serving as the main campuses for international students in Malaysia and having more than 40 new international postgraduates in their first semester in Malaysia. For students, only new international postgraduates entering the selected universities in their first academic semester will be eligible to participate.

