#### Secondary Outcomes: Adjustment and Intention to Drop Out

Adjustment is known as a short-term and dynamic process experienced by the individual in relation to the new cultural environment; it also refers to the degree to which a certain university meets the demands or requirements of international students [107-109]. According to Ward and Kennedy [110], there are two dimensions of adjustment: sociocultural and psychological.

First, sociocultural adjustment is a process in which individuals with different cultural backgrounds become skilled and able to engage in negotiating the host culture and effectively interacting with its local people [111]. Assessment of the individual’s sociocultural adaptation is based on a 20-item version of the Sociocultural Adaptation Scale (SCAS) [110]. Participants will be asked questions regarding the degree of difficulty experienced by them in a number of areas [110,112-115]. This is based on a 5-point Likert scale for rating the difficulty of 20 daily situations adapted by the participating international students in the Malaysian context. Initial use of the SCAS was documented in a previous study that indicated it was reliable, with scale alphas ranging from .75 to .91, indicating good internal consistency and construct validity [110-115]. The SCAS is regarded as a flexible research instrument and measure that is easily modified based on characteristics of the sojourning sample, and it can be adapted to different cultural contexts [34].

Second, the Satisfaction with Life Scale (SWLS) is used to measure psychological adjustment and the cognitive component of subjective well-being [116] through 5 items. Consistent with the standpoint of the World Health Organization on health, psychological adjustment is seen as state of well-being and not merely the absence of disease [117]. Hence, its specific focus is on evaluating individuals’ perceived satisfaction with life as a whole based on their criteria and views [118,119]. The items on the SWLS are based on a 5-point scale on which respondents are asked to agree or disagree with 5 statements (eg, “In most ways my life is close to my ideal”). The scale is available in a range of languages and has been used in cross-cultural research [118], and its internal consistency for psychological adjustment has proved to be very good [34,42,109,119].

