### Statistical Analysis

We will use SPSS Statistics version 25.0 (IBM Corp) to analyze the data. Statistical significance will be considered as a *P* value of less than .05. Analysis of the data will take into account clustering of students within universities. The study will use statistical analyses, including descriptive statistics of the respondents’ sociodemographic characteristics, chi-square test for nonparametric variables, and 2-tailed *t* test for continuous variables, to compare between the control and intervention groups on sociodemographic variables and primary and secondary outcome measures. Complete case analyses, intent-to-treat analyses, and completer status analyses will be conducted according to the initial allocation of universities to either intervention or control groups. In relation to the missing data, we will follow the guidelines for analyzing and reporting cluster RCTs with missing data established by Fiero et al [141] and Díaz et al [142].

The effectiveness of the intervention will be assessed using the generalized estimation equation (GEE). Specifically, the differences in the research hypothesis in terms of students’ acculturative stress, adjustment (sociocultural and phycological), and intention to drop out will be compared at 3 points—time 1 (preintervention), time 2 (immediately postintervention), and time 3 (3-month follow-up)—between and within the intervention and the control groups adjusted for covariate variables. The GEE method was chosen because of its efficiency in appropriately modeling the structure of the correlations of the pre-post repeated measures and its low degree of reliance on the assumption of normality in the distributions of data for the variables in the analysis. Furthermore, in the context of RCT research, multilevel models such as the GEE are the most appropriate model because they permit the estimation of treatment effects (ie, group differences) across multiple time points within a single statistical model [143].

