However, there is no default option in the GEE analysis for eta squared to obtain the intervention effect size that can be expressed as a standardized effect size. Therefore, two popular measures, Cohen d and eta squared, will be used in this study. Cohen d = beta ÷ standard deviation, with beta representing the difference between two means for the two groups relative to their standard deviation obtained from the pooled variance to compute the effect size within group and between group [144-146]. Hence, d = (mean 1 – mean 2) / (the average standard deviation of the two groups). The eta squared indicates how much of the total variance is explained by the difference between the means. Therefore, we will convert the effect size d to eta squared with the equation η^2^=d^2^/d^2+4^. The reported effect size d is also interpreted by Cohen [147] as adopted by many previous studies, specifically intervention as well in terms of the practical or clinical significance of the effect, 0.2 (small effect), 0.5 (moderate effect), and 0.8 (large effect), and similarly for eta squared 0.01 (small effect), 0.06 (moderate effect), and 0.14 (large effect) [146,148-151].

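### Hypothesis 2 gives before-after change in the intervention arm equal standing with the randomised comparison as evidence of effect, so change that would occur without the programme could be read as benefit

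*Protocol article*

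**What the plan says.** Under Study Hypothesis, the protocol article lists two hypotheses side by side, both said to serve the study's objectives. The first is between arms: "the intervention group will score significantly higher than the wait-list group on the immediate and 3-month postintervention evaluation". The second is within the intervention arm: "scores for the intervention group at the immediate and 3-month postintervention follow-up will be significantly higher than scores of the baseline". It does not mention the wait-list arm.

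The objective behind both is aim 3 under Study Aims, to "determine the effect of the educational intervention on acculturative stress, adjustment, and intention to drop out between and within the control and intervention groups". Three further places keep the two kinds of comparison in parallel:

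- The Results paragraph of the abstract: "significant differences between and within groups are determined as" P<.05.
- Statistical Analysis, where effectiveness is to be assessed by comparing outcomes over three time points "between and within the intervention and the control groups adjusted for covariate variables".
- The effect-size text in the same section, where Cohen d is used "to compute the effect size within group and between group" and then read against benchmarks for practical or clinical significance.

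On the population, the Participants section says that "only new international postgraduates entering the selected universities in their first academic semester will be eligible to participate". On one of the secondary outcomes, the protocol says: "Adjustment is known as a short-term and dynamic process experienced by the individual in relation to the new cultural environment".

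**The concern.** A change from baseline in one arm combines the programme's effect with everything else that happens over the same months: settling in, academic calendar, repeated questionnaires, regression to the mean. The wait-list arm is there to remove these, and hypothesis 2 does not use it. For newly arrived students, followed to three months after the programme, some change without the programme is plausible.

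If both arms changed equally, hypothesis 1 would show no difference while hypothesis 2 could still be significant. The protocol does not say which result then decides whether the programme worked. A positive within-arm result, with a within-group Cohen d beside it, could be reported as effectiveness without contradicting anything in the plan.

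**Working it through.** **The plan's own figure first.** Inputs from Sample Size: means 2.58 and 2.07 (difference 0.51) and SD 1.08. Power is not stated in the text; 80% with two-sided 5% gives n = 2 × (1.960 + 0.842)² × 1.08² / 0.51² ≈ 70.4, so 71 per arm. The design effect is 1 + (40 − 1) × 0.05 = 2.95. Then 71 × 2.95 = 209.45, taken as 209 per arm; 209/0.8 = 261.25, taken as 261; and 2 × 261 = 522. The stated figures reproduce. The calculation is for a between-arm difference, so it concerns hypothesis 1, not hypothesis 2.

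**How often hypothesis 2 is satisfied with no programme effect.** Work in SD units and let s be a drift common to both arms.

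- n = 209 analysed in the intervention arm (protocol).
- D, the variance inflation of the mean change: 1 (none) or 2.95 (the protocol's design effect applied in full). The protocol gives no figure for clustering of change, so these are used as a bracket.
- r, the baseline to follow-up correlation: 0.3, 0.5 or 0.7 (assumed).
- s: 0.1 or 0.2 SD (assumed).

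SE = √(2(1 − r)D/n). Rejection probability = Φ(s/SE − 1.96) + Φ(−s/SE − 1.96).

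For example, with r = 0.5 and D = 1, SE = √(1/209) = 0.069. At s = 0.2, s/SE = 2.89 and the probability is 82%. With D = 2.95, SE = √(2.95/209) = 0.119, s/SE = 1.68 and the probability is 39%.

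| Drift | r | D = 1 | D = 2.95 |
|---|---|---|---|
| 0.1 SD | 0.5 | 30% | 13% |
| 0.2 SD | 0.3 | 69% | 30% |
| 0.2 SD | 0.5 | 82% | 39% |
| 0.2 SD | 0.7 | 96% | 58% |

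The nominal rate is 5%. With s = 0 the formula returns 5%, so the excess comes from the drift alone.

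**The between-arm contrast under the same drift.** If both arms move by s, the difference in change is s − s = 0, and a valid between-arm test keeps its 5% level whatever s is.

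**Sensitivity to the reference distribution.** The section on randomization speaks of ten universities. If they split five and five, a t reference on 4 degrees of freedom lowers the figures. At r = 0.5 they become 20% (D = 1) and 10% (D = 2.95) for 0.1 SD, and 59% and 26% for 0.2 SD. All stay above 5%.

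**The case against.** The strongest reply is that the randomised comparison is already in the plan. Hypothesis 1 compares the arms at both follow-ups. Statistical Analysis justifies the GEE by its ability to estimate treatment effects as group differences over time. The abstract's Conclusions state the expected stress result as a difference from the wait-list group. This stands: a reader might infer that the trial discards its randomised comparison, and the protocol does not support that. The fault lies in hypothesis 2 and in the parallel standing given to it.

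A reader might also infer that the trial will declare an effect when change is significant in one arm and not in the other. No section states such a rule. Aim 3 covers both arms, so change in the control arm would be visible as well.

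The direction of the wording is a further limit. Hypothesis 2 says scores will be *higher*. On the acculturative stress scale a higher total means more stress, and a higher likelihood of withdrawal is also worse. Read literally, a natural fall in stress would not satisfy hypothesis 2. The point holds for the evident intent, improvement from baseline, and literally for satisfaction with life, where higher is better.

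Finally, the support for drift is modest. The description of a short-term, dynamic process concerns adjustment, a secondary outcome, and gives neither direction nor size. Nothing in the protocol says that acculturative stress changes during the first semester without intervention; enrolment at arrival makes it plausible, no more.

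None of this removes the core. No section confines within-group tests to description, and none says that the between-arm result decides.

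**Conclusion.** The point holds in a limited form. Hypothesis 2 is a formal test of change in one arm, placed under an aim to determine the intervention's effect and given equal standing with the randomised comparison. It cannot distinguish a programme effect from change over time that would have happened anyway. Hypothesis 1 and the GEE reduce the harm but do not settle which result governs.

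The rejection rates with zero programme effect, about 13–30% at 0.1 SD drift and 30–96% at 0.2 SD, are illustrations. They rest on assumed drift and correlation, on 209 analysed students, on a normal reference, and on a bracket for clustering from no inflation to 2.95. They show that a small common drift is enough to matter; they do not predict what this trial will find. The direction error in the hypotheses should be corrected as a separate matter.

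**What to change.** Remove hypothesis 2 as a test of effectiveness. State that the claim of effectiveness rests only on the between-arm contrast from the planned GEE, either group-by-time or a baseline-adjusted difference, at the immediate and 3-month follow-ups. Bring aim 3, the abstract and the effect-size text into line. Report within-arm changes and within-group effect sizes for both arms, with confidence intervals, as description.

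The cost is wording. The contrast comes from the model already planned, fewer P values need reporting, and the sample size does not change because its calculation is already between arms.
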